### Interventions

#### Scheme of standard analgesic use

Postoperatively, patient-controlled analgesia will be used until postoperative day (POD) 3. The used analgesic will be fentanyl (Yichang Renfu Pharmaceutical Co. Ltd., Yichang, China) at a continuous infusion rate of 0.25 μg/(kg h) and a bolus of 0.15 μg/kg with a 10-min lockout time. The locking duration of the projectile will be 10 min after administration. Further, oral celecoxib capsules (Pfizer Pharmaceutica Co. Ltd., New York State, USA) will be provided to the participants on demand between the POD 4 and POD 14. Moreover, additional analgesia consumption will be recorded.

#### Basic physical therapy

Both groups will undergo basic post-surgery physical therapy (exercise) from 24 h after TKA. The programme will be supervised by a physical therapist and involve ankle pumping exercises, hip flexion (straight leg raise), and pain-free knee mobilization in flexo-extension. The exercises will be performed daily at 30-min sessions for 2 weeks. Additionally, the participants performed ankle pumping exercises with the lower extremities elevated and respiratory exercises for the first 24–48 post-TKA hours.

#### EA group

Based on the new standard of “International Acupuncture Nomenclature” [29], the LIANGQIU (Stomach 37, ST37), ZUSANLI (Stomach 36, ST36), XUEHAI (Spleen 10, SP10), and YINLINGQUAN (Spleen 9, SP9) acupoints on the surgery side will be employed (Fig. 4). After skin disinfection, adhesive pads (size 8 × 10 mm, Suzhou Medical Supplies Factory, Suzhou, China) will be placed on the acupoints through which acupuncture needles (size 0.25 × 40 mm, Suzhou Medical Supplies Factory, Suzhou, China) will be inserted approximately 3 cm into the skin (Fig. 4). After achieving de qi sensation, the acupuncture points will be stimulated using Huatuo SDZ-II EA apparatus (Suzhou Medical Supplies Factory, Suzhou, China). The intensity of the constant current square wave pulse at a frequency of 40 Hz and a pulse width of 1 ms will be gradually increased until it reached an intolerable intensity. The treatment of the EA group will involve ten 30-min sessions over 2 weeks (5 sessions per week).

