### Eligibility criteria

The inclusion criteria will be as follows: (1) 60–80 years of age, (2) diagnosed with KOA and willing to undergo unilateral TKA, (3) undergone similar surgical approach with normal blood coagulation function, (4) having posterior cruciate-stabilizing prostheses (Smith & Nephew, London, UK), (5) having well-placed knee prosthesis (as shown by the postoperative X-ray), and (6) postoperative clear consciousness and normal cognitive function.

The exclusion criteria will be as follows: (1) serious nervous system problems, cardiovascular diseases, osteoporosis, and metabolic diseases; (2) having coagulation disorder, haemophilia, or tumour; (3) intraoperative bone fracture, dislocation, and structural abnormality; and (4) skin damage in the acupoint area.

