### Exit criteria and management

Exit criteria include (1) participant request, (2) severe postoperative complications (e.g. pulmonary embolism), and (3) intratreatment side effects.

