### Outcome evaluations

The primary outcomes will include muscle strength and the Hospital for Special Surgery (HSS) score. The secondary outcomes will include the 4-m walk test (4 MWT), numerical rating scale (NRS), and the Hamilton Anxiety Scale (HAM-A) score. Further, additional analgesia use will be considered a secondary outcome. Additional outcome indexes will include the incidence of analgesia-related side effects and participant satisfaction rate.

The NRS score, additional analgesia use, and incidence of EA-related and analgesia-related side effects will be recorded daily. Evaluation of EA discomfort and acceptance will be conducted after the first day of EA intervention. Muscle strength will be evaluated at two time points, i.e. before surgery and at 2 weeks after EA intervention. The HSS score, 4 MWT, and HAM-A score will be evaluated at four time points, i.e. before surgery, before the EA intervention (at POD 3), 1 week after EA intervention, and 2 weeks after EA intervention.

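### The electroacupuncture current is titrated to an intolerable level as written; this is probably a slip for the maximum tolerable level, but nothing in the article corrects it

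*Protocol article*

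**What the plan says.** The EA group section under Interventions in the Protocol article places the needles on the operated limb ("acupoints on the surgery side will be employed"). It fixes the waveform as a constant-current square wave at 40 Hz with a 1 ms pulse width. For strength, its only instruction is that the intensity "will be gradually increased until it reached an intolerable intensity". Treatment is ten sessions of 30 minutes in two weeks.

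The patients are "60–80 years of age" and must have "postoperative clear consciousness and normal cognitive function" (Eligibility criteria). The Outcome evaluations section has an assessment "before the EA intervention (at POD 3"), which puts the first EA session at about that day.

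**The concern.** The sentence is operative Methods text and defines where the ramp stops. As worded, it stops only once the patient can no longer tolerate the stimulus. An operator who follows it exactly takes a recently operated older patient past the limit of tolerance. Someone replicating the trial would have to guess whether a comfortable, a strong but bearable, or a maximum tolerable level was meant.

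The concern is limited to that stopping point. The sentence does not say that the level reached is then held for the session, and no such reading is needed. Nothing is claimed about a missing current ceiling, withdrawal rates, blinding or the size of the treatment effect.

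**Working it through.** No formula applies, and the plan has no figure to reproduce. The check was to look through the whole article for anything that sets, limits or corrects the stimulation intensity.

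**Is another end point stated anywhere?**
- Abstract: gives acupoints and session numbers, and nothing on intensity.
- EA group: gives frequency, pulse width and the sentence at issue. It has no step-back, current value or tolerance limit.
- Sham EA group: describes wires with no output, so it contains no titration rule to compare.
- Adverse events of EA: lists mainly needling complications and adds events during the strength and walk tests. It sets no stimulation limit.
- Discussion: mentions intensity only in general terms.
- Figures (not shown): the captions concern the recovery pathway, trial flow, schedule, acupoint location, needle type and depth, satisfaction and blinding. None suggests an intensity rule.

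The sentence therefore stands alone, and nothing overrides it.

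**Does the rest of the article fit the literal wording?** It does not fit well.
- The text closing the Sham EA group section says no harm is expected from taking part.
- Exit criteria and management makes side effects during treatment a reason to leave the trial.

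Both provisions sit awkwardly with an end point the patient cannot bear, which supports reading the phrase as a slip.

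**What do the safeguards do?**
- The increase is gradual, and participants who are conscious and cognitively normal can ask for it to stop.
- Withdrawal is open to them ("Exit criteria include (1) participant request").
- The "incidence of EA-related and analgesia-related side effects will be recorded daily".
- How patients find the treatment is also assessed, once day 1 is over.

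The first limits any overshoot while it happens. The others act through withdrawal or by recording what has already occurred. None restates where the ramp should end.

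**To whom does it apply?** The Abstract plans 94 participants, and Randomization and blinding allocates 47 per group. The sentence governs the EA arm: 47/94 = 50%. This counts the people covered and does not measure harm.

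**The case against.** The strongest reply is that this is a language slip that no operator would act on. The phrase also has a tense error. The article reverses its meaning in another place too: the Discussion describes the control wires as having electrical output, where the Sham EA group section says they have none. Raising a current until a limit is reported is also an ordinary way to find a threshold. On that reading the practical difference is at most the last step of a gradual ramp, which an alert patient can halt. Finally, the article condenses a full protocol that is not shown, so the operators' own document may be correct.

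Much of this stands. A slip is the likeliest explanation, any overshoot would probably be brief, and it is not known what the operators were given. But the threshold reading has to be supplied by the reader, because no step back to a tolerable level is written. Nor is the point about something the article leaves out: it states an end point and states it wrongly. A correct full protocol would not make the published sentence right.

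**Conclusion.** The point holds. The only intensity rule in the article is wrong as written, and no other section corrects it. It covers the 47 participants planned for EA. The article offers no basis for putting a number on harm, so none is given, and no sample size, power or alpha figure depends on the wording.

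Confidence that the wording is wrong is high. Whether operators received the same wording cannot be judged from this article. Because the sentence concerns patient safety and costs almost nothing to correct, it should be corrected, though the safeguards keep it from being a grave defect.

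**What to change.** In the EA group section, replace the end point with: *will be gradually increased to the maximum intensity the participant can tolerate, and reduced if it becomes intolerable*. If the full protocol specifies a different tolerable level, use that wording.

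Check that the operators' instructions agree, and brief them before the first participant. The Trial status section dates recruitment from 1 August 2020, and the article was published on 10 August 2020. If treatment has already begun, brief them before the next session.

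The cost is one phrase and a short briefing. Design, sample size, sham procedure and analysis are unchanged.

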**Fig. 4 Fig4:**
[figure not shown]
Location of acupoints for the EA and the sham EA groups

#### Sham EA group

In the sham EA group, sham EA using a pragmatic placebo needle [30] (size 0.25 × 30 mm) will be applied on sham acupoints for 5 sessions per week. Each sham acupoint will be at 1 cun (≈ 20 mm) lateral to the acupoints (Fig. 5). The pragmatic blunt-tipped placebo needle will be inserted into the adhesive pads without skin penetration (Fig. 4). A Huatuo SDZ-II EA apparatus (Suzhou Medical Supplies Factory, Suzhou, China) will be connected to the sham acupoints through special electrode wires without electricity output. The sham needles will remain in the adhesive pads for 30 min in each session. The sham EA and EA treatment processes are similar except the former does not involve skin penetration, needle manipulation, and electric output.

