**Methods/design:**

This is a double-blinded, randomized, and controlled trial. It will be conducted between August 2020 and December 2020. Ninety-four participants with KOA who have undergone unilateral TKA will be randomized into a treatment (EA) group and a control (sham EA) group. The former and latter groups will receive EA and sham EA, respectively, at ST37, ST36, SP10, and SP9 acupoints. The participants will undergo ten treatment sessions over 2 weeks (5 sessions per week). The primary outcomes will include changes in muscle strength and the Hospital for Special Surgery score at the second week from baseline (pre-op 1 day or POD 3). The secondary outcomes will include a 4-m walk test, numerical rating scale score, the Hamilton Anxiety Scale score, and additional analgesia use. Additional outcomes will include the incidence of analgesia-related side effects and the participant satisfaction rate. Participant blinding will also be assessed where they will be asked to guess whether they received EA after the latest intervention. Adverse EA events will be documented and assessed throughout the trial.

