### Randomization and blinding

Independent research staff will use RV.3.5.1 software to generate a randomly numbered sequence for complete random grouping. A number sequence will be sealed by an independent assistant in an opaque envelope containing treatment information. Eligible and consenting patients with KOA who have undergone unilateral TKA will be randomly assigned to the EA and sham EA groups at a ratio of 1:1 (each group, *n* = 47). Only the physiotherapist in charge of EA treatment is authorized to open the envelope and enrol participants.

All the participants, physiotherapists, outcome assessors, and data statisticians will be subject to blinding. To help maximize participant blinding, a pragmatic placebo needle will be employed and a sham EA design will be applied. Unblinding before study completion will only be allowed in the case of medical emergencies or severe adverse events.

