#### Hospital for Special Surgery score

The Hospital for Special Surgery (HSS) score was developed by John N. Insall, the father of the modern artificial knee joint. It was first used in 1976 for pre- and postoperative evaluation of four different types of knee arthroplasty prostheses and is reliable and effective [31]. The HSS score includes 10 main items for the comprehensive evaluation of the condition of participants with respect to pain, daily activity, range of knee motion, muscle strength, deformity, and instability. The score will be used to evaluate the participants’ pre- and post-TKA knee joint function to evaluate the EA effect on early rehabilitation. Its components will be further analysed to identify factors that can promote patient rehabilitation.

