### Adverse events of EA

EA-related complications will mainly refer to broken needles, halo acupuncture, stagnation acupuncture, hematoma at the acupuncture site, continuous post-needling pain lasting > 2 h, bleeding, etc. Moreover, we will record the adverse events during the tests: knee muscle strength using IST and 4MWT.

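### EA punctures the skin beside the knee being rated and sham does not, yet the masking measures and the blinding check are aimed only at participants, so assessor blinding is at risk

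*Protocol article*

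**What the plan says.** **EA arm.** Under EA group, "acupoints on the surgery side will be employed", and 0.25 mm needles "will be inserted approximately 3 cm into the skin". On dose, "The treatment of the EA group will involve ten 30-min sessions over 2 weeks (5 sessions per week)".

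**Sham arm.** Under Sham EA group, "The pragmatic blunt-tipped placebo needle will be inserted into the adhesive pads without skin penetration". The sham points lie about 20 mm lateral to the real ones. The section itself names skin penetration as one of the differences between the arms.

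**Blinding.** Randomization and blinding lists outcome assessors among those blinded. The device it then describes has a narrower purpose: "To help maximize participant blinding, a pragmatic placebo needle will be employed and a sham EA design will be applied". Under Blinding assessment, a questionnaire after the last session goes to participants only.

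**Assessment.** Muscle strength and HSS are the primary outcomes. HSS covers, among other domains, "range of knee motion, muscle strength, deformity, and instability". For peak torque, the physiotherapist seats and fixes the participant and aligns the machine's axis with the knee.

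**Local signs.** Adverse events of EA lists "hematoma at the acupuncture site" and bleeding among the complications to be recorded. It gives no frequencies.

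**The concern.** The chosen sham creates a physical sign that can exist in only one arm, and it sits on the limb the assessor rates. Non-penetrating needles and pads can keep participants from knowing their arm. They do nothing about what an assessor may see on the skin afterwards.

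The stake is observer bias in a primary outcome. Range of motion, deformity and instability are judged by an examiner looking at or handling the operated knee. An assessor who suspects the arm could shade those items without intending to. Changing who holds the allocation or the case report forms would not remove this cue, because an otherwise independent assessor still sees the leg.

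**Working it through.** **Step 1: count the insertions.** The article states no such figure, so there is none to reproduce. Inputs: four acupoints (Abstract, "at ST37, ST36, SP10, and SP9 acupoints") and ten sessions (EA group), assuming one insertion per acupoint per session.

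- EA, end of treatment: 4 × 10 = 40. After the first week: 4 × 5 = 20.
- Sham: 0 throughout.

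Forty is an upper bound on insertions, not a number of marks. The same four sites are needled repeatedly, and early punctures may have healed.

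**Step 2: count the positions that could differ.** Four acupoints plus four sham points 20 mm lateral make eight. The Abstract reads as though both arms use the named acupoints. The location difference rests on the Sham EA group section. The penetration difference does not depend on it.

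**Step 3: match the exposure to the visits** (Outcome evaluations).

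| Outcome | Post-treatment assessments | Examiner's influence |
|---|---|---|
| HSS | week 1 and week 2 | rates the knee directly |
| Peak torque | week 2 only | positions the limb; the machine gives the reading |

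The timing is ambiguous. The Abstract puts the primary endpoint at the second week from baseline, which is at or near the last session. Outcome evaluations speaks of 2 weeks after EA intervention, which could mean two weeks after the last session, when marks may have faded.

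**Step 4: illustrate what a bias would do.** Suppose there is no true effect and the EA mean is shifted by *b* standard deviations. For one two-sided *t* test at 5% with *n* per arm, the false-positive rate is P(|T| > t₀.₉₇₅) with 2n − 2 degrees of freedom, where T is non-central *t* with non-centrality b√(n/2). Take n = 40, since 47 × 0.85 = 39.95, and compare with the full 47.

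| Assumed shift *b* | n = 40 | n = 47 |
|---|---|---|
| 0.10 | 7.3% | 7.7% |
| 0.15 | 10.2% | 11.1% |
| 0.20 | 14.3% | 16.0% |
| 0.30 | 26.3% | 30.2% |

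The shift is an average over the whole EA arm. If marks were noticed in a fraction *p* of EA participants and moved the score by *s* SD when noticed, then b = p × s. For example, 0.5 × 0.30 = 0.15. The article supplies neither *p* nor *s*, so the table is a range under assumption, not an estimate for this trial.

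**The case against.** The strongest reply is that this is a journal article. Whether the knee is dressed or covered at assessment is working detail that the full protocol may hold, and its absence here is no fault in itself. That is right. A reader might infer that assessors see the knee bare, but the article does not say so. The point rests instead on what is stated: a sham that differs in skin penetration, assessors declared blind, and masking described in some detail with participants as its stated target.

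Other parts of the objection also stand:

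- **Visibility is inferred.** The needles are 0.25 mm wide and no rate of marks is given. The knee has also just been operated on, so small marks may be hard to tell from surgical ones (an inference, not in the article).
- **Listing haematoma is not predicting it.** A reader might take the adverse-event section to expect bruising. It only names what will be recorded, and elsewhere the article anticipates no harm from taking part.
- **There is no week-1 strength test.** Torque is exposed after treatment only at 2 weeks. The primary comparison is set at the second week, so a week-1 cue does not decide it.
- **The false-positive figures are generic.** They would apply to any bias of that size in any trial of this size.
- **A firmer threat to blinding lies elsewhere.** The physiotherapist in charge of EA opens the envelope, physiotherapists are declared blind, and an unspecified physiotherapist runs the strength test. If these are one person, covering the skin achieves nothing.

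None of this removes the arm-specific cue. It limits how much can be claimed for it.

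**Conclusion.** The concern holds as a risk to assessor blinding, not as a demonstrated failure of it. The difference of up to 40 insertions against none on the rated limb follows from the text. So does the lack, in the article, of any described measure or check directed at assessors. The risk is mainly to HSS at the week-1 and week-2 visits. For peak torque it is smaller, confined to handling and effort at 2 weeks.

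A reader might go further and conclude that marks reveal the EA arm, or that both primary outcomes are biased towards EA. The document does not support either: it gives no frequency of visible marks and no basis for the size or direction of a scoring shift. The risk shrinks if the final assessment comes two weeks after the last session. The point is worth acting on because the remedy costs almost nothing and supports blinding the article already claims.

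**What to change.** 1. Before each post-treatment HSS assessment and the 2-week strength test, existing non-assessor staff place identical small opaque dressings over the same eight positions (four acupoints and four sham points) in both arms. Use separate dressings, because a sleeve could affect motion or torque measurement.
2. The assessor does not remove them. Existing non-assessor staff inspect the sites for adverse events.
3. The assessor records a guess of the arm at week 2, reported next to the participants' guesses.
4. Reconcile Randomization and blinding with the Muscle strength section, so that it is clear the assessor is not the treating physiotherapist who opens the envelope. Without this, items 1 to 3 do not help.
5. State whether the 2-week assessment is counted from the start or the end of treatment.

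**Cost.** About a minute and a few dressings per assessment, one extra case report form item, and no extra visit or staff. The downside is less direct skin inspection by the assessor.

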**Fig. 5 Fig5:**
[figure not shown]
Difference of acupuncture needle and acupuncture depth between the two groups. **a** The tip of the pragmatic placebo needle (left) is blunt. **b** The pragmatic placebo needle (left) to be inserted into the sterile adhesive pads, but with no skin penetration. The acupuncture needle (right) to be inserted through the sterile adhesive pads into the skin

To ensure compliance with treatment, participants will be required to register for treatment. Throughout the trial, the participants will be treated separately to prevent inter-participant communication. Implementing EA or sham EA will not affect usual care pathways (including the use of any medication), which will continue for both groups. There is no anticipated harm and compensation for trial participation.

### Outcome evaluations

The primary outcomes will include muscle strength and the Hospital for Special Surgery (HSS) score. The secondary outcomes will include the 4-m walk test (4 MWT), numerical rating scale (NRS), and the Hamilton Anxiety Scale (HAM-A) score. Further, additional analgesia use will be considered a secondary outcome. Additional outcome indexes will include the incidence of analgesia-related side effects and participant satisfaction rate.

The NRS score, additional analgesia use, and incidence of EA-related and analgesia-related side effects will be recorded daily. Evaluation of EA discomfort and acceptance will be conducted after the first day of EA intervention. Muscle strength will be evaluated at two time points, i.e. before surgery and at 2 weeks after EA intervention. The HSS score, 4 MWT, and HAM-A score will be evaluated at four time points, i.e. before surgery, before the EA intervention (at POD 3), 1 week after EA intervention, and 2 weeks after EA intervention.

